#### 8.4.2. Action taken with study treatment

If action is taken with respect to a study drug in order to resolve the SAE, the action is to be documented using the following categories:

- Temporary interruption
- Definitive interruption
- None
- Dose changed
- Unknown

#### 8.4.3. Other specific treatment(s) of serious adverse events

- None
- Remedial drug therapy
- Other

#### 8.4.4. Outcome

The outcome of the SAE is to be documented using the following categories:

- Recovered/resolved
- Recovering/resolving
- Recovered/resolved with sequelae
- Not recovered/not resolved
- Fatal
- Unknown

#### 8.5. Assessments and documentation of adverse events

All AEs occurring from the time the subject has signed the ICF until 30 ( $\pm 7$ ) days after the last dose of study drug (Safety Follow-up) must be entered in the subject's eCRF and coded according to CTCAE v 4.0.

Documentation of an AE must be supported by an entry in the subject's medical file.

#### 8.6. Expected adverse events

For this study, the applicable reference document is the most current version of the IB.

Overview listings of frequent events that have occurred so far in the clinical development are shown in the current IB. If relevant new safety information is identified, the information will be integrated into an update of the IB and distributed to all participating sites.

The expectedness of AEs will be determined by the Sponsor according to the applicable reference document and according to all local regulations.

#### 8.7. Procedures for safety reporting

The coordinating centre at NCI Naples will:

- review all adverse and serious adverse events reported in the Study and issue queries directly to the Investigator reporting the event
- determine if event qualifies as a SUSAR
- report all SUSARs to the national regulatory authority Agenzia Italiana del Farmaco (AIFA), to all Participating Investigators, and to Ethics Committees of participating centres within the timelines of the article 17 of the European Directive 2001/20/EC.
- provide an annual safety reports, including all Serious Adverse Events occurring in the Study, to all Participating Investigators, to Ethics

Committee of participating centres and to the national regulatory authority Agenzia Italiana del Farmaco (AIFA).

### *Reporting flow for SAEs and SUSARs*

[figure not shown]

## 8.8. Pregnancies

The investigator must report to the coordinating centre any pregnancy occurring in a study subject during the subject's participation in this study. The report should be submitted within the same timelines as an SAE, although a pregnancy per se is not considered an SAE.

For a study subject, the outcome of the pregnancy should be followed up carefully, and any outcome of the mother or the child should be reported.

If cases of drug exposure via the father are reported, all efforts should be made to obtain information on course and outcome of the pregnancy, subject to the partner's consent.

For all reports, the forms provided are to be used.

## 9. STATISTICAL ANALYSIS

All the analyses will be descriptive. Patients will be defined as evaluable if they have assumed at least one regorafenib tablet.

### 9.1 Primary endpoint

The rate of patients alive and not progressed at 6 months is the primary study end-point. This rate will be calculated by dividing the number of evaluable patients alive and not progressed after 6 months from study entry, by the number of enrolled evaluable patients. Exact 95% confidence intervals will be described.

The following will be considered as events:

- progression of disease at any date within 6 months from registration, according to RECIST criteria (including deterioration of clinical conditions that prevent radiological restaging);
- death for any cause within 6 months from registration;
- interruption of regorafenib due to adverse events followed by initiation of an alternative antineoplastic treatment within 6 months from registration.

If drug-related adverse events lead to definitive termination of regorafenib but the clinical condition of the patient does not require immediate switch to a different antineoplastic treatment, the patient can be followed according to protocol schedule and will be defined as success or failure according to the time of disease progression as above.

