#### 4. STUDY DESIGN

This is a multicentre, single-arm, phase 2 study according to Simon's two-stage optimal design. This design has been applied to minimize the number of patients exposed to a possibly inactive drug, considering that alternative treatment options exist, although not satisfactory and likely to be more toxic. Patients who will receive at least one dose of study drug will be considered evaluable.

The primary endpoint will be the rate of evaluable patients alive and not progressed at 6 months.

The sample size calculation is based on the following statistical parameters:

- minimum acceptable rate of patients alive without progression at 6 months ( $p_0$ ) = 30%;
- auspicated rate ( $p_1$ ) = 50%
- type I and II errors = 10%.

According to these parameters, 22 evaluable patients should be enrolled at the first stage and the study will proceed to the second stage if at least 8 patients will be alive without progression after 6 months. At the second stage, further 24 evaluable patients will be enrolled for an overall sample of 46 evaluable patients. The study will be considered positive if at least 18 patients out of 46 will be alive without progression at 6 months. It is planned that 5 to 10 centres will participate in the study, which could be completed in 24 months.

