## 6. STUDY PROCEDURES

### 6.1 Screening visits/procedures

Screening procedures may be completed during multiple visits but must be completed within the specified timeframes before the first dose of study drug.

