| Coagulation panel                         | X                | X                                  |                                 |
| GFR calculation                           | X                |                                    |                                 |
| AST, ALT and bilirubin                    | X                | X                                  |                                 |
| Drug accountability                       | X                |                                    |                                 |
| Survival status                           |                  |                                    | X                               |

AE = adverse event, ALT = alanine aminotransferase, AST = aspartate aminotransferase, CEA = carcinoembryonic antigen, CBC = complete blood count, CRC = colorectal cancer, CT = computed tomography, ECG = electrocardiogram, ECOG = Eastern Cooperative Oncology Group, ID = identification, GFR = glomerular filtration rate, EORTC QLQ-C30 = European Organization for Research and Treatment of Cancer Quality of Life C30 questionnaire, EQ-5D-3L = European Quality of Life Group five dimensions questionnaire 3-level version, ICF = informed consent form, MRI = magnetic resonance imaging, PET = positron emission tomography, PRO = Patient-reported Outcomes.

1 From cycle 3 to the end of treatment, visit on D15 may be scheduled at the discretion of the investigator, if scheduled, visits on D15 should include the same procedures as were performed on D15 C2 (expecting for the plasma biomarker sampling)

- Screening procedures may be completed during multiple visits but must be completed within specified timeframes before the first dose of study drug..
- ICF must be signed before any study-related procedures are performed (including screening procedures); this will include consent for tumor tissue collection (primary tumor

and liver metastases) as well as a separate ICF for molecular analyses of whole blood.

- c. All CT/MRI scans (chest, abdomen, pelvis, and other suspected sites as applicable) to determine eligibility for randomization must be performed with 4 weeks prior to randomization
- d. CT/MRI scans (chest, abdomen, pelvis, and other suspected sites as applicable) will be performed at week 6th and the 12nd week: after CT/MRI scans will be performed at 3-month intervals until disease recurrence as assessed by the investigator.

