- e. 18FDG-PET CT scan on day 14 (+/-2) after treatment start (results will not be communicated to the patient and the treating physician)
- f. ECG, physical examination, and laboratory evaluations are not required on Cycle 1, Day 1 if performed within 7 days of initiation of study drug.
- g. After 6 cycles, ECG may be performed at the investigator's discretion. ECG must be performed at End-of treatment.
- h. AE assessment is to be started from signing of ICF until 30 days after the last dose of study drug (Safety Follow-up) and at the discretion of the investigator (serious adverse events only) during Active and Survival Follow-up
- i. Platelet count ( $\geq 100,000$  cells/mm^3), hemoglobin concentration ( $\geq 9$  g/dL), and absolute neutrophil count ( $\geq 1500$  cells/mm^3) without transfusion or granulocyte-colony stimulating factor and other hematopoietic growth factors must be met at study entry
- j. CEC and CEP counts, blood samples to be stored for evaluation of cytokines, circulating angiogenic factors and miRNA plasma levels will be performed on day 14th +/-2 after starting treatment, before starting the 2nd cycle ( day 28) at the first restaging ( after 6 weeks) and at progression of the disease.
- k. Female subjects of childbearing potential must have a negative pregnancy test result  $\leq 7$  days prior to randomization.
- l. A urinalys by dipstick, and a microscopic analysis if the urine dipstick tests shows a change from normal
- m. GFR  $> 30$  mL/min/1.73 m^2 according to the Modified Diet in Renal Disease abbreviated formula
- n. Subjects who are therapeutically treated with an agent such as warfarin or heparin will be allowed to participate if no underlying abnormality in coagulation parameters exists per medical history. If a subject is taking warfarin or heparin with stable PT-INR at baseline, close monitoring of PT-INR and aPTT should be performed  $\geq 1$  times/week until PT-INR and aPTT are stable as compared with a pre-dose measurement (defined by the local standard of care)
- o. Only if subject is maintained on warfarin or heparin

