## 7. RESPONSE EVALUATION

Response must be evaluated through repetition of the CT scan of chest, abdomen and pelvis at week 6th and 12nd from treatment start and thereafter every 3 months.

Response will be codified by the Investigator according to the RECIST (Response Evaluation Criteria In Solid Tumours) guidelines version 1.1, summarised below.

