## 14. PERSONAL DATA PROTECTION PROCEDURES

In order to protect the *privacy* of patients enrolled in the study, the following procedures will be used:

- the Coordinating Center, which has centralized responsibility for registration, randomization and data collection and processing procedures, will not allow access to the data, except to public authorities responsible for inspections under the relevant legislation (Health Ministry, Ethics Committee);
- at registration, patients will be assigned a numerical identification code (corresponding to progressive numbers of patients enrolled in the study) that will be noted together with the participating center's code for all the CRFs (web or paper based) and that will be used in all communications regarding individual patients;
- a list of patient codes and names will be kept by the Participating Investigator Center;
- documents that are not for submission to the Coordinating Center (eg, signed informed consent forms) should be kept in strict confidence by the investigator.

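### The 6-month endpoint runs from registration but CT/MRI runs from treatment start; the third scan has about 8 days of slack at most, and a later one can turn a progression into a success

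*Protocol*

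**What the plan says.** Section 9.1 uses a date-based rule. A patient fails on "progression of disease at any date within 6 months from registration, according to RECIST criteria", on death within the same period, or on starting another antineoplastic treatment in that period after stopping regorafenib for an adverse event. Clinical deterioration that prevents restaging counts as progression. The numerator is worded slightly differently, as evaluable patients "alive and not progressed after 6 months from study entry".

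The scans use another origin. Section 7 places CT at weeks 6 and 12 "from treatment start and thereafter every 3 months". Table 6, note d, repeats this: "after CT/MRI scans will be performed at 3-month intervals until disease recurrence as assessed by the investigator". No scan is tied to the 6-month landmark, and Section 9.1 has no rule for a third scan done after it.

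The lag from registration to first dose is not fixed. Section 14 says that "at registration, patients will be assigned a numerical identification code", and Table 6 lists ID allocation in the day -28 screening column. Section 6.1 requires only that screening procedures "must be completed within the specified timeframes before the first dose of study drug".

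**The concern.** The endpoint and the assessment that supplies it are measured from different days, and the third scan falls close to the landmark. Small slippage moves it past 6 months. Read literally, the event rule then does not count a progression first documented on that scan, and nothing else requires the patient to have been shown progression-free at 6 months. Success would rest on the week-12 scan.

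A late scan can only turn a failure into a success. This is a single-arm study with no control group to share the delay, and the decision is a fixed count of at least 18 of 46, so each patient is worth 1/46 = 2.2 percentage points. The result could depend in part on appointment dates.

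**Working it through.** **1. The design as stated.** Inputs from Section 4: p0 = 0.30 (the "minimum acceptable rate of patients alive without progression at 6 months"), p1 = 0.50, both errors 10%; continue with at least 8 of 22; positive with at least 18 of 46.

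P(positive | p) = Σ over x = 8 to 22 of P(X₁ = x) × P(X₂ ≥ 18 − x), with X₁ ~ Bin(22, p) and X₂ ~ Bin(24, p).

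This gives 0.097 at p = 0.30 and 0.905 at p = 0.50. The stated design reproduces. (Section 9.3 gives a different first-stage rule; that is a separate matter and is not used here.)

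**2. The dates.**
- Third scan: 84 + 91 = day 175 from first dose.
- Landmark: 6 × 30.44 = 182.6, about day 183 from registration.
- Slack if registration and first dose fall on the same day: 183 − 175 = 8 days. With real calendar months it is 5 to 9 days, mean 7.3.
- If 3 months means 12 weeks: 84 + 84 = 168, and 182.6 − 168 = 14.6 days.
- The fourth scan, at 84 days plus 6 months, is at about day 267 and cannot help.

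**3. Effect of a lag.** Margin = 7.3 − (lag + scan delay).

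| Lag plus delay (days) | Margin (days) |
|---|---|
| 0 | +7.3 |
| 3 | +4.3 |
| 7 | +0.3 |
| 14 | −6.7 |
| 28 | −20.7 |

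The protocol gives neither the lag nor the delay; these values are assumed.

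**4. Patients exposed.** Assume a constant hazard with a true 6-month rate of 30%: S(t) = 0.30^(t/183).
- S(84) = 0.575, so 0.575 − 0.300 = 27.5% progress between week 12 and month 6.
- S(175) = 0.316, so 0.575 − 0.316 = 25.9% could be found by an on-time third scan. The other 1.6 points progress after day 175, and an on-time scan misses them anyway.

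**5. Effect on the decision.** Let f be the share of third scans dated after the landmark (assumed).
- Upper bound: apparent rate = 0.30 + f × 0.275, with nothing caught by other means.
- Half caught: apparent rate = 0.30 + f × 0.259 / 2, with half of the exposed progressions caught by death, clinical deterioration or an end-of-treatment scan (assumed).

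Putting each rate into the formula in step 1:

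| f | Rate, half caught | P(positive) | Rate, upper bound | P(positive) |
|---|---|---|---|---|
| 0 | 30.0% | 9.7% | 30.0% | 9.7% |
| 10% | 31.3% | 13% | 32.8% | 18% |
| 25% | 33.2% | 20% | 36.9% | 37% |
| 40% | 35.2% | 29% | 41.0% | 58% |

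**6. Effect of judging status on a landmark scan.** Same model, all scans on day d: rates 0.30^(d/183) and 0.50^(d/183).

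| d | Rate at p0 | Type I error | Rate at p1 | Power |
|---|---|---|---|---|
| 183 | 30.0% | 9.7% | 50.0% | 90.5% |
| 189 | 28.8% | 7% | 48.9% | 88% |
| 196 | 27.5% | 4.8% | 47.6% | 84.8% |

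**The case against.** Followed to the day with little start lag, the schedule works: the third scan precedes the landmark by about a week. The problem needs a delay, and the protocol gives no figure for one. A reader might infer from ID allocation in the day -28 column of Table 6 that registration precedes dosing by up to four weeks, so that even punctual scans are usually late. The documents do not establish this. Table 6 counts its screening columns back from enrolment, while Section 6.1 counts the same windows back from first dose, which suggests the two days were treated as nearly the same.

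A reader might also take it as certain that a progression seen just after 6 months is a success. The event rule says so, but the numerator wording ("alive and not progressed after 6 months from study entry") leaves room to exclude that patient. The text is ambiguous, so the supportable word is may.

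Existing safeguards count. Deaths and deterioration within 6 months are failures, the end-of-treatment assessments include CT/MRI, and Section 6.4 has scans collected for possible review of progression timing. The 30% benchmark may itself come from scan-based assessment, in which case part of the delay is already in it.

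The lack of a CT window, in contrast to PET ("18FDG-PET CT scan on day 14 (+/-2) after treatment start"), is not a fault by itself, because windows and late-scan handling are often left to the SAP, which is not at hand.

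All of this limits the size of the effect and the certainty about it. It does not remove the mismatch: the scan calendar and the event rule are both fixed in the protocol, and an SAP cannot supply a landmark scan that the schedule does not require.

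**Conclusion.** The point holds as a mismatch of clocks with little slack: at most about 8 days, or about 15 if 3 months means 12 weeks. Beyond that, success may rest on a week-12 scan, and the error runs only towards a positive trial.

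The dates are firm; the inflation is not. At a true rate of 30%, a false-positive chance of about 13%, 20% or 29% is plausible if 10%, 25% or 40% of third scans are late and half of the exposed progressions are caught otherwise. The 18%, 37% and 58% figures are upper bounds and should not be read as the trial's actual type I error. Both sets assume a constant hazard and late shares that the protocol does not give.

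It should be corrected, because the go/no-go count depends on it and the remedy is mainly wording.

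**What to change.** Amend Sections 7 and 9.1 and Table 6, note d:

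1. Use one origin for both the endpoint and the scans. Registration or treatment start would serve, since every evaluable patient has taken at least one tablet; use one term for it throughout Section 9.1.
2. Tie the third CT/MRI to the landmark, at 26 weeks from that origin, with a narrow window (for example ±1 week), for every patient not yet progressed.
3. State in Section 9.1 that 6-month status is taken from this scan, so progression on it is a failure even if dated a few days after 6 months, and that success requires this scan or a later one without progression.

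**Cost.** No scan is added; the third moves by about a week. Scans late within the window lower the observed rate slightly: if every one fell at day 189, power would be about 88% and type I error about 7%. Patients with no landmark or later scan, and no earlier event, would count as failures. A window running to week 28 would overcorrect: with all scans at day 196, power would fall to 84.8% and type I error to 4.8%.

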## 5. TREATMENT PLAN

### 5.1. Regorafenib treatment

Patients will receive regorafenib orally 160 mg once daily for the first 3 weeks of each 4-week cycle.

Treatment will be definitively stopped in case of disease progression, unacceptable toxic effects, motivated decision to stop the treatment by the treating physician, or refusal or withdrawal of consent by the patient.

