### 9.2. Secondary endpoints

- Toxicity: for each patient and for each type of toxicity, the worst degree suffered during treatment will be described.
- Objective response rate: defined as the number of complete plus partial responses divided by the number of patients enrolled.
- Progression free-survival: defined as the time from registration to progression or death without progression, whichever occurred first. Patients without progression at the end of the study will be censored at the date of the last visit when eventual progression was verified.
- Overall survival: defined as the time from registration to the date of death due to any cause. Patients still alive at the end of the study will be censored on the date of the last information on vital status.
- Metabolic response: defined as a reduction  $\geq 50\%$  of SUVmax after 2 weeks of treatment.

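### Section 9.1 scores a switch to another anticancer treatment as failure only after an adverse-event stop, so a patient who switches after a physician-decision or patient-request stop can count as a regorafenib success

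*Protocol*

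**What the plan says.** Section 9.1 defines the primary endpoint as the proportion of evaluable patients alive and not progressed at 6 months, and lists three events that make a patient a failure. The first is RECIST progression, which includes clinical deterioration that prevents restaging. The second is death from any cause. The third is "interruption of regorafenib due to adverse events followed by initiation of an alternative antineoplastic treatment within 6 months from registration". The paragraph after the list deals with patients who stop for drug-related adverse events and do not need to switch at once. They stay on the protocol schedule and are scored by when they progress.

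Stopping is allowed on wider grounds than progression and toxicity. Section 5.1 adds "motivated decision to stop the treatment by the treating physician, or refusal or withdrawal of consent by the patient", and Section 5.3 lets the patient decline further treatment without giving a reason. Section 5.5.1 bars other anticancer therapy only while study treatment is running. Section 6.3 (Follow-up) then asks for subsequent treatment to be recorded and for tumour and vital status every 3 months. One tablet makes a patient evaluable (Sections 4 and 9), so nobody who switches leaves the denominator.

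The decision rule is in Section 4: "22 evaluable patients should be enrolled at the first stage and the study will proceed to the second stage if at least 8 patients" are alive without progression, and then "The study will be considered positive if at least 18 patients out of 46 will be alive without progression at 6 months".

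**The concern.** The third event shows that the sponsor does not want disease control under a new drug credited to regorafenib. The rule is then applied to only one route off treatment. Suppose two patients each stop at month 2 without progression, start the same irinotecan-based regimen and are progression-free at month 6. If the first is recorded as stopping for an adverse event, that patient is a failure. If the second is recorded as stopping by physician decision or own request, that patient is a success.

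The route is a practical one. Everyone enrolled is irinotecan-naive (Section 3.3), and Section 1.1 names irinotecan-based chemotherapy as the alternative for these patients at progression, so an unused next line is available. The investigator who records the reason for stopping knows the treatment and the patient's course. What is at stake is the go/no-go conclusion: activity of the next line could help regorafenib reach 18 of 46.

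**Working it through.** **1. Is the switch covered anywhere?** Taking each reason for stopping, followed by a new anticancer treatment and no progression by month 6:

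| Reason for stopping | Event under 9.1? |
|---|---|
| Progression, or deterioration preventing restaging | Yes, first event |
| Adverse event, drug-related or not | Yes, third event |
| Intercurrent illness | Normally yes: Section 8.1 defines an adverse event without requiring a causal link |
| Second primary cancer | Yes: Section 8.2 makes it reportable as a serious adverse event |
| Physician decision with no adverse event | No |
| Patient request or refusal with no adverse event | No |
| Withdrawal of consent to follow-up | Not addressed; a missing-data question |

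The open cases are the physician-decision and patient-request stops.

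**2. Reproduce the design.** Inputs from Section 4: p0 = 30%, p1 = 50%, both errors 10%, continue with at least 8 of 22, positive with at least 18 of 46. With X1 ~ Bin(22, p) and X2 ~ Bin(24, p),

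P(positive | p) = Σ over x = 8 to 22 of P(X1 = x) · P(X2 ≥ 18 − x).

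This gives 0.0974 at p = 0.30 and 0.9049 at p = 0.50. A full search for the Simon optimal design returns the same 22/46 plan. (Section 9.3 states a different first-stage rule. That is a separate matter; the Section 4 rule is used here.)

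**3. Effect of the gap when the true rate is 30%.** Let x be the share of patients who switch by an uncovered route, and s the share of those who are progression-free at month 6. The documents give neither. If switchers would otherwise have had the same 30% rate as everyone else, the rate the trial would score is

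p* = 0.30(1 − x) + s·x.

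If instead every switcher is progression-free and none would have been without the switch, p* = 0.30 + x.

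| x | Assumption | p* | P(positive) |
|---|---|---|---|
| 0 | no switchers | 0.300 | 9.7% |
| 5% (about 2 of 46) | s = 0.5 | 0.95 × 0.30 + 0.025 = 0.310 | 12.5% |
| 5% | s = 1 | 0.285 + 0.05 = 0.335 | 21.4% |
| 5% | s = 1, none otherwise a success | 0.350 | 27.9% |
| 10% (about 5 of 46) | s = 0.5 | 0.90 × 0.30 + 0.05 = 0.320 | 15.7% |
| 10% | s = 1 | 0.27 + 0.10 = 0.370 | 37.7% |
| 10% | s = 1, none otherwise a success | 0.400 | 53.2% |

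**4. Effect of the consistent rule.** If every such switch is a failure, the scored rate is p(1 − x). At x = 5% it is 0.285 when the true rate is 30%, with P(positive) 6.4%. When the true rate is 50% it is 0.475, with P(positive) 84.5% against 90.5%.

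**The case against.** The strongest reply is that the residual group is small and its size unknown. A reader might infer that every stop other than a toxicity stop is uncovered. It is not: the third event says adverse events without requiring a drug relation, so intercurrent illness, second cancers and allergic reactions already fall under it. This stands, and the point is limited accordingly.

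A reader might also infer that such a patient is certain to enter the numerator. Section 5.3 promises those who decline treatment follow-up for safety and survival, Table 6 lists only survival status in that phase, and its notes accept telephone contact. Section 6.3 (Follow-up) does ask for tumour status every 3 months, so a documented success is possible but not assured.

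Third, ignoring or counting a treatment switch is a choice of estimand, and counting every switch biases the other way. In addition, Section 5.5.1 groups surgery and radiotherapy with antineoplastic therapies, so a patient resected after shrinkage on regorafenib could become a failure. The warning about resection stands and must be dealt with in the fix. The estimand argument does not rescue the text. A rule that ignores switches would have no third event, and a composite rule would apply it to all switches. Section 9.1 does neither.

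Finally, it is tempting to say that PFS in Section 9.2 will disagree with the primary endpoint, because PFS follows patients through later therapy and does not repeat the clinical-deterioration clause. The documents do not support this. Section 9.2 does not redefine progression, so the meaning in 9.1 can carry over. Its censoring rule, "Patients without progression at the end of the study will be censored at the date of the last visit when eventual progression was verified", is compatible with a legitimate PFS that ignores switches. A further PFS sensitivity analysis can be left to the SAP.

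**Conclusion.** The point holds in a limited form. Under the written event list, a patient who stops without an adverse event, progression or deterioration preventing restaging, switches, and is documented alive and progression-free at month 6 is a regorafenib success. The same course with an adverse event recorded as the reason is a failure. Relative to a consistent rule, the gap can only add successes.

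Its size cannot be read from the protocol. At an assumed 5% of patients and a true rate of 30%, the chance of a positive study is between 12.5% and 27.9% instead of 9.7%, depending on how many switchers are progression-free and how many would have been anyway. These figures illustrate; they are neither forecasts nor bounds, and at a lower switching frequency the effect shrinks. A result of exactly 18 of 46 would turn on one such patient (17 of 46 is 37.0%), but any threshold rule has that property, so it is no separate evidence of harm.

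This is not a detail left to the SAP, since the protocol itself fixes the event list and restricts it. A SAP that broadened the list would contradict the protocol.

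**What to change.** Reword the third event in Section 9.1 along these lines: *start of any alternative antineoplastic treatment within 6 months of registration, whatever the reason regorafenib was stopped*. In the same place, state how resection or other local treatment of responding disease is scored. Make the change before any 6-month outcome is assessed. In Section 9.2, at most add that PFS uses the same definition of progression as 9.1.

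The change needs no new data, because subsequent treatment is already collected under Section 6.3 (Follow-up). The sample size and the thresholds of 8 of 22 and 18 of 46 stay as they are. The cost is a slightly lower observed rate, because some switchers who would have stayed progression-free are counted as failures. At an assumed 5% of such switchers and a true rate of 50%, power falls from 90.5% to 84.5%; with fewer switchers the loss is smaller.
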